## Abstract

**Background: **Comprehensive geriatric assessment (CGA) has been shown to improve outcomes in hospitalised older adults; however, there is currently no compelling evidence to support CGA interventions within the Emergency Department (ED). The aim of this study is  to explore the clinical and process outcomes of older adults who receive ED-CGA over a period of six months after their initial ED attendance.

**Design: **Prospective cohort study.

**Methods: **The STrengthening the Reporting of the OBservational studies in Epidemiology (STROBE) standardised reporting guidelines will be adhered to. Older adults aged ≥65 years who score ≥2 on the Identification of Seniors at Risk (ISAR) tool and present to the ED with a medical complaint during the operational hours of the dedicated interdisciplinary team, will be considered eligible for recruitment. Demographic and health assessment information will be obtained at the ED index attendance followed by completion of an interdisciplinary CGA. A dedicated research nurse will complete follow-up telephone interviews with participants at 30 days and six months. The primary outcome will be incidence of hospital admission from the ED index attendance. Secondary outcomes will include functional decline, patient satisfaction with the ED index attendance, unscheduled ED reattendance(s), unscheduled hospital (re)admission(s), nursing home admission(s), healthcare utilisation, and death. Descriptive statistics will be used to profile the characteristics of the study participants and multivariate logistic and linear regression analysis will be used to analyse risk of adverse outcomes.

**Ethics and dissemination: **Ethical approval was granted by the
University of Limerick Hospital Group Research Ethics Committee (107/2021). The authors will disseminate study findings through publication in a peer-reviewed journal and presentation at national and international conferences. Patient and public involvement will be sought from a panel of older adults at the Ageing Research Centre in the University of Limerick.

**Clinicaltrials.gov Identifier:** NCT05252182.

## Introduction

The significant growth in ED attendances is a growing public health issue (
Morley *et al.*, 2018), with attendances by older adults accelerating exponentially, beyond that due to population ageing alone (
Lowthian *et al.*, 2015). The most obvious causative factor for older adults increased aggregate demand for healthcare, specifically ED usage, is the clinical condition of frailty (
Clegg *et al.*, 2013). The presence of diminished homeostatic reserves leaves older adults more susceptible to acute exacerbations of comorbid and long-term conditions, which result in a concomitant increased demand for emergency and urgent care services (
Vermeiren *et al.*, 2016). There is unequivocal agreement within the literature that the ED is a challenging environment to deliver effective care to frail older adults (
Baum & Rubenstein, 1987). The complexity underlying the nature of their presenting complaint, which is often non-specific in nature may complicate ED care (
Salvi *et al.*, 2007) and investment in additional time and resources is frequently indicated to deliver a holistic assessment across multiple domains (
Limpawattana *et al.*, 2016). This can be challenging in the context of ED time-based targets, which have historically been designed for persons with single system illnesses and robust social networks (
Hommick *et al.*, 2016). Emergency medicine (EM) staff training has predominantly focused on clinically urgent and diagnostic specific complaints, thus creating a mismatch between the ED response and the changing demographic that they are increasingly facing (
Conroy & Turpin, 2016).

An ED attendance is often considered a sentinel event for an older adult (
Sanders *et al.*, 1996), with associated functional decline, increased risk of unplanned 30-day ED reattendance, and mortality well documented (
Lowthian *et al.*, 2016;
Nagurney *et al.*, 2017;
Shen *et al.*, 2018). Conversely, it affords clinicians an opportunity to stratify a high risk cohort followed by delivery of a holistic and bio-psychosocial intervention to mitigate against suboptimal clinical and process outcomes. These interventions include, but are not limited to, interface geriatrics and CGA, health and social care professionals (HSCP) and/or nursing interventions, and ED case management and post-discharge services referrals/liaison (
Cassarino *et al.*, 2019;
Conroy *et al.*, 2011;
Lowthian *et al.*, 2015). CGA is considered more effective than usual care in improving a range of outcomes for hospitalised frail older adults (
Ellis *et al.*, 2017). Evidence exists to support the feasibility of embedding CGA within the ED (
Conroy *et al.*, 2014) and an interdisciplinary model of care whereby clinicians integrate geriatric competencies into their practice has been recommended to meet the emergency needs of this patient population (
Conroy & Turpin, 2016).

Despite this recommendation, there is no robust high quality evidence that ED-CGAs are effective at improving clinical and process outcomes.
Conroy *et al.* (2011) conducted a systematic review and meta-analysis of five randomised controlled trials (RCT), which evaluated the role of CGA in older adults being rapidly discharged from the ED or Acute Medical Unit. They found no compelling evidence to support implementation of CGA interventions in this patient cohort in terms of mortality [risk ratio (RR) 0.92, 95% confidence interval (CI) 0.55 to 1.52], readmissions [RR 0.95, 95% CI 0.83 to 1.08)], institutionalisation, functional status, quality-of-life or cognition. More recently,
Harding (2020) provided an overview of five studies, which measured the impact of ED-CGAs on secondary healthcare utilisation, specifically 30-day ED reattendance and hospital admission. Two RCTs, one case matched cohort study, and two quasi-experimental pre and post intervention studies were reviewed. No definitive evidence was found to support the hypothesis that ED-CGAs can reduce ED reattendance or hospital admission 30 days post index attendance. We propose to explore the clinical and process outcomes of older adults who receive an interdisciplinary ED-CGA over a period of six months after their initial ED attendance through the conduct of a prospective cohort study.

## Methods

### Study design

The STROBE standardised reporting guidelines will be followed in the conduct and reporting of this prospective cohort study (
Von Elm *et al.*, 2007). Participant data collection and follow-up will take place between February 2022 to January 2023 (inclusive). 

### Ethics

Ethical approval for the study was granted by the Research Ethics Committee, Quality and Safety Department, University of Limerick Hospital Group Hospital (Ref: 107/2021). In accordance with the Data Protection Act 2018 (Section 36(2)
Health Research Board, 2018), written informed consent will be obtained from eligible participants.

### Setting

The study setting will be the ED of University Hospital Limerick (UHL), which is a university teaching hospital with a large catchment area in the Mid-West of the Republic of Ireland. UHL is the central hub for a larger hospital group with six hospital sites, all functioning as a single hospital system caring for a substantially rural population of approximately 400,000. The university teaching hospital is the only hospital in the group that has a 24/7/365 emergency care and critical care service and has 455 inpatient beds. 76,667 ED attendances were recorded in 2021 of which 19,901 were older adults aged ≥ 65 years.

### Population of interest

Older adults aged ≥ 65 years who present to the ED of UHL (Monday-Friday, 08:00-16:00) between February 2022 and July 2022 will be deemed eligible for recruitment provided they meet the following criteria:

**
*Inclusion criteria*
**. We will include older adults aged ≥ 65 years who have a Manchester Triage System (MTS) category of 2 to 5 (
Mackway-Jones, 1997) and are presenting with a medical complaint. Eligible participants will be identified by a member of the interdisciplinary ED-CGA team and must screen positive for risk of adverse outcomes on the ISAR tool. The ISAR is composed of six simple yes/no items; a score of ≥ 2 indicates that the older adult is at increased risk of adverse outcome following ED index presentation (
McCusker *et al.,* 1999).

**
*Exclusion criteria*
**. Exclusions to recruitment will apply where older adults are deemed not to have decision-making capacity to provide informed consent or if attendance to the ED is outside of the operational working hours of the interdisciplinary ED-CGA team. Those presenting with acute cardiac and/or neurological pathology; injuries requiring surgical intervention; or high illness acuity, which necessitates treatment in the resuscitation room throughout their ED attendance, will be excluded.

### Recruitment and data collection

**
*ED index attendance*
**. A dedicated research nurse or clinical member of the interdisciplinary ED-CGA team will provide prospective participants with an information leaflet and explain the objective of the study. If the participant agrees to take part, he/she will be asked to read and sign a consent form. After consenting to recruitment, each participant will undergo a baseline assessment inclusive of a demographic questionnaire and a health assessment. Demographic information will include participant’s gender, age, marital status, residential status (living alone, living with others, nursing home resident, other), ethnicity, socioeconomic status (level of education, past/present occupation), mode of arrival to the ED (private transport, ambulance, public transport, other), source of referral (self-referral, general practitioner, out of hours general practitioner, injury unit, nursing home, etc), index complaint and triage category as per the MTS (
Mackway-Jones, 1997). The health assessment will comprise of the following measurements: the 21-item Charlson Comorbidity Index score (
Charlson *et al.*, 1994) to profile baseline comorbidities; a list of medications; a global measure of functional ability through the self-rated Barthel Index (BI) for activities of daily living (
Mahoney & Barthel, 1965); delirium and cognitive screening through the 4AT (
Bellelli *et al.*, 2014); health-related quality of life through the EuroQoL survey 5-dimension and 5-levels form (EQ-5D-5L) (
Rabin & de Charro, 2001); frailty status through Rockwood’s Clinical Frailty Scale (
Rockwood *et al.*, 2005); and nutritional status through the Malnutrition University Screening Tool (MUST) (
Elia & Russell, 2009).

Following baseline assessment, participants will undergo an interdisciplinary CGA across multiple domains including medical, functional, cognitive, and psychosocial abilities (
Rubenstein *et al.*, 1991). The interdisciplinary team will compromise a registrar in geriatric medicine, specialist geriatric nurse, senior occupational therapist, senior physiotherapist, and senior medical social worker with dual governance from consultants in EM and Geriatric Medicine. Interventions delivered by the interdisciplinary team will include, but not limiting to, patient and family education on the outcome of the CGA and ED discharge plan; a review of diagnoses; medication reconciliation; prescription of enabling equipment to compensate for unresolved functional deficits; provision of home exercise/activity programmes and patient and family education on self-management strategies, as appropriate. Members of the team will be guided by their clinical expertise and competencies, scope, and codes of professional practice. Individualised care planning and referrals to out-of-hospital pathways, as appropriate will be the forefront of the teams’ practice. Where older adults are referred to specialist geriatric ambulatory care hubs, the focus will be on completing the priority domains and components of CGA in the ED with timely completion of the assessment in its entirety in the specialist hubs, within seven days of referral.

**
*Follow-up assessment*
**. The research nurse will complete follow-up telephone interviews with participants at 30 days and six months. He/she will complete the 18-item Patient Satisfaction Questionnaire (
Marshall & Hays, 1994) at 30-day follow-up to explore participants’ satisfaction with their ED attendance. The BI (
Mahoney & Barthel, 1965) and EQ-5D-5L (
Rabin & de Charro, 2001) will be completed with participants in addition to a questionnaire, which will look specifically at capturing healthcare utilisation e.g. geriatric ambulatory care services, GP visits, public health nurse visits, home care support, outpatient clinic attendance, HSCP input etc. The questionnaire will follow the same structure and outline as the prospective cohort study conducted by
Leahy *et al.* (2020). Data on objective measures such as unscheduled ED reattendance, hospital (re)admission(s), nursing home admission, and death will be ascertained from routine hospital data. Withdrawals and participants lost to follow-up will be recorded.

### Outcome variables

The primary outcome measure will be incidence of hospital admission from the ED index attendance. Secondary outcomes include functional decline (including functional decline at discharge among the admitted cohort), patient satisfaction with the ED index presentation, incidence of unscheduled ED reattendance(s), unscheduled hospital (re)admission(s), nursing home admission(s), healthcare utilisation, and death within 30 days and six months of the ED index attendance.

### Sample size

All prospective participants that meet inclusion criteria will be invited to participate. The primary outcome of interest will be incidence of hospital admission of the participants post exposure to the interdisciplinary ED-CGA team. In order to detect a reduction in the admission rate of at least 25%, at 5% level of significance and with 80% power, we would require 128 participants.

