### Statistical analyses

Pseudonymised data will be stored on an encrypted and password protected electronic data capture system (CASTOR). Members of the research team who have responsibility for entering pseudonymised participant data, will have their own unique log in and password for the system. Hard copies of baseline and follow-up questionnaires and consent forms will be stored in a locked cabinet in an office with restricted access.

Descriptive statistics will be used to profile the baseline characteristics of the cohort. Categorical measures (e.g., rates of 30-day ED reattendance) will be analysed in terms of frequencies and percentages; continuous measures (e.g., Barthel Index) will be analysed in terms of mean and standard deviation for normally distributed data and as median and interquartile ranges for non-parametric data. Multivariate logistic and linear regression analysis will be used to analyse risk of adverse outcomes and we will report adjusted RR or beta coefficients with 95% CI. Anonymised data generated will be published in an open access repository with an associated data dictionary

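### The sample size claims 80% power to detect a 25% reduction in admissions, but the plan has no comparator, reference rate or test for a reduction

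*Protocol article*

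**What the plan says.** The Sample size section of the protocol article gives one justification for the number of participants: "detect a reduction in the admission rate of at least 25%, at 5% level of significance and with 80% power, we would require 128 participants". It does not say what rate the reduction is measured from, whether 25% is relative or absolute, which test applies, or whether the 5% is one- or two-sided.

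Elsewhere the article describes a different kind of study:

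- **Aim (Abstract).** To "explore the clinical and process outcomes of older adults who receive ED-CGA over a period of six months after their initial ED attendance". The Introduction repeats this: "We propose to explore the clinical and process outcomes of older adults who receive an interdisciplinary ED-CGA over a period of six months".
- **Primary outcome (Outcome variables).** "The primary outcome measure will be incidence of hospital admission from the ED index attendance".
- **Exposure (Recruitment and data collection).** All participants have the interdisciplinary CGA after their baseline assessment. No other group is recruited or drawn from records.
- **Analysis (Statistical analyses).** Categorical measures are summarised as counts and percentages. Beyond that, "Multivariate logistic and linear regression analysis will be used to analyse risk of adverse outcomes".
- **Setting.** The numbers of ED attendances in 2021 are given, overall and for those aged 65 and over. No admission rate is given.

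**The concern.** Power is a property of a specified test of a specified contrast, and here neither is specified. Because everyone is exposed, the regression models cannot contain an ED-CGA term, so they can only relate patient characteristics to outcome. A percentage of patients admitted, reported alone, is not a test of reduction either.

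This matters because admission is the primary outcome, and the Introduction describes the evidence for ED-CGA as inconclusive. A statement of 80% power to detect fewer admissions invites readers to take an uncontrolled proportion as a powered test of whether ED-CGA reduces admission. The article also leaves open which benchmark the observed rate would be compared with, so one could be chosen after the data are seen.

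**Working it through.** **Inputs from the Sample size section:** reduction 25%, significance level 5%, power 80%, N = 128. **Not given:** reference rate p0, scale of the 25%, design of the test, sidedness. Every p0 below is therefore an assumption.

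**1. Can 128 be reproduced from the stated inputs?** No, because p0 is missing. It can be matched by supplying p0 and a test. Two examples follow; neither should be read as the derivation actually used.

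*One-sample, two-sided test, relative reduction (p1 = 0.75·p0):*

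n = [1.96·√(p0(1−p0)) + 0.8416·√(p1(1−p1))]² / (p0−p1)²

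At p0 = 0.49, p1 = 0.3675:

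n = [1.96 × 0.4999 + 0.8416 × 0.4821]² / 0.1225² = 127.9

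*Two equal groups, two-sided, absolute 25-point drop:* the total with continuity correction is about 128 at p0 = 0.48 and about 130 at p0 = 0.49. Without the correction the total peaks at 124.

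Other matches exist for a relative 25% reduction: a one-sided one-sample test with p0 near 0.42–0.43, or 128 per group (two-sided) with p0 near 0.68–0.69. So 128 does not identify the intended calculation.

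**2. How far does the claimed power depend on the missing rate?** For the one-sample reading with N = 128:

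power = Φ{[(p0−p1)·√128 − 1.96·√(p0(1−p0))] / √(p1(1−p1))}

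At p0 = 0.50, p1 = 0.375: (0.125 × 11.314 − 1.96 × 0.5) / 0.4841 = 0.897, and Φ(0.897) = 0.82.

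| Assumed p0 | n for 80% power | Power with 128 |
|---|---|---|
| 30% | 278 | 45% |
| 40% | 182 | 65% |
| 50% | 124 | 82% |
| 60% | 85 | 93% |

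**3. If 128 were meant as two groups of 64** (not the design described, shown only because the sentence does not exclude it), with the pooled-variance test and a relative 25% reduction:

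| Assumed p0 | Total N for 80% power | Power with 64 per group |
|---|---|---|
| 40% | 712 | 22% |
| 50% | 492 (494 with whole patients per group) | 30% |
| 60% | 346 | 40% |

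**4. What a single cohort of 128 can deliver.** The 95% CI half-width is 1.96·√(p(1−p)/128):

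- p = 0.50: 1.96·√(0.25/128) = 0.087, or 8.7 percentage points
- p = 0.30: 1.96·√(0.21/128) = 0.079, or 7.9 percentage points

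**5. Is any of these tests planned?** No. The Statistical analyses section contains no test against a fixed rate and no between-group comparison.

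**The case against.** The strongest reply is that a single cohort can be tested against a fixed benchmark, and that 128 is right for such a test if the benchmark is about 49%. On that view the number may be correct, and the article has merely left the reference rate and the test to a fuller document. It can be added that the stated aim is exploratory, that no causal conclusion is promised, that all eligible attenders are invited so 128 may be only a minimum, and that the two-group figures concern a design nobody proposed.

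Part of this stands. The figure 128 is not shown to be arithmetically wrong. The one-sample range straddles 80%, so it shows dependence on an unstated input and does not show that the study is underpowered. The two-group figures illustrate the ambiguity of the sentence and are not a criticism of the design.

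The reply does not remove the problem. The point is a conflict between two things the article does state: a sample size built on detecting a reduction, and an aim and analysis confined to describing one exposed cohort. A fuller analysis plan could add a benchmark test, but the analysis as set out does not include one. If the aim is only exploratory, the power sentence is the part that is wrong.

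**Conclusion.** The concern holds and should be corrected. As written, the 80% power is attached to a test that does not appear in the plan, and it cannot be verified from the document. Under a two-sided one-sample test of a relative 25% reduction, power with 128 runs from 45% to 93% as the assumed reference rate goes from 30% to 60%. What the described design supports is an estimate of the admission proportion, to within about 8 to 9 percentage points at rates of 30% to 50%, and an exploration of patient-level predictors. It does not support a powered statement about a reduction. The absence of a comparator, reference rate and matching test is read directly from the text; the power figures rest on assumed rates and normal approximations.

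**What to change.** **Preferred.** Delete the power sentence and justify 128 by precision: a 95% CI of about ±8.7 percentage points around an admission rate of 50%. In the Statistical analyses section, name the primary analysis as the admission proportion with its 95% CI, and state that no reduction attributable to ED-CGA will be inferred. This costs wording only and needs no extra patients; the price is giving up the power claim.

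**If the comparison is to be kept.** Name the reference rate and its source (for example the site's own rate in comparable attenders), say whether 25% is relative or absolute, state sidedness, add the matching test to the analysis section, and label the comparison non-causal. Recalculate N at the named rate. For a two-sided one-sample test of a relative reduction, 128 suffices at about 49% or above, but 182 would be needed at 40% and 278 at 30%, so this route may need more participants. Data collection is described as ongoing, so record the benchmark and its source before the admission results are examined.

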### Statistical analyses

Pseudonymised data will be stored on an encrypted and password protected electronic data capture system (CASTOR). Members of the research team who have responsibility for entering pseudonymised participant data, will have their own unique log in and password for the system. Hard copies of baseline and follow-up questionnaires and consent forms will be stored in a locked cabinet in an office with restricted access.

Descriptive statistics will be used to profile the baseline characteristics of the cohort. Categorical measures (e.g., rates of 30-day ED reattendance) will be analysed in terms of frequencies and percentages; continuous measures (e.g., Barthel Index) will be analysed in terms of mean and standard deviation for normally distributed data and as median and interquartile ranges for non-parametric data. Multivariate logistic and linear regression analysis will be used to analyse risk of adverse outcomes and we will report adjusted RR or beta coefficients with 95% CI. Anonymised data generated will be published in an open access repository with an associated data dictionary

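### Logistic regression is paired with an adjusted risk ratio, but its coefficients give odds ratios and no step from one to the other is stated

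*Protocol article*

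**What the plan says.** The only inferential analysis in the Statistical analyses section is the sentence "Multivariate logistic and linear regression analysis will be used to analyse risk of adverse outcomes and we will report adjusted RR or beta coefficients". Confidence intervals are to be given at the 95% level. The Abstract names the same two regression types and no others.

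The abbreviation RR is defined once, in the Introduction, where a published meta-analysis is quoted with a "risk ratio (RR) 0.92" for mortality. RR therefore means risk ratio in this document.

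The outcome that matters most is binary: "The primary outcome measure will be incidence of hospital admission from the ED index attendance". Secondary outcomes that are binary, or can be analysed as such, include ED reattendance, hospital (re)admission, nursing home admission and death. No expected rate is given for any of them. The Sample size section refers to "a reduction in the admission rate of at least 25" per cent, "at 5% level of significance" and 80% power, and concludes that "we would require 128 participants", without a baseline admission rate.

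**The concern.** The sentence joins two models to two effect measures. Linear regression goes with beta coefficients, which are its direct output. By the same pattern a reader will take adjusted RR to be the direct output of logistic regression, and it is not. The article mentions no odds ratio, no standardisation or conversion, and no log-binomial or Poisson model. The stated model and the stated measure do not match without a step that is not there.

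At stake is how the adjusted results are read. The Discussion addresses clinicians, policymakers and funders, who will take an RR as a ratio of risks. If the exponentiated coefficient were printed under that label, a moderate rise in the risk of a common outcome could be read as a doubling or more.

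**Working it through.** **Inputs.** From the article: logistic regression for binary outcomes; RR meaning risk ratio; a binary primary outcome; n = 128 with 5% significance, 80% power and a 25% reduction. Not in the article: any admission rate. The reference risks below are assumptions.

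**Does the stated sample size reveal the admission rate?** Not uniquely. The text does not say whether the 25% is absolute or relative, whether the test is one- or two-sided, or whether one or two samples are compared. Several readings give 128:

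- One sample, two-sided, 25% relative reduction from 0.49 to 0.3675: n = [1.96·√(0.49·0.51) + 0.8416·√(0.3675·0.6325)]² / 0.1225² = (0.9798 + 0.4058)² / 0.01501 ≈ 127.9, so 128.
- Two groups, two-sided, continuity-corrected, 25 points absolute: 0.47 against 0.22, or 0.78 against 0.53, each 64 per group, 128 in total.
- Two groups, one-sided, 25% relative: 0.80 against 0.60, 64 per group, 128 in total.

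Over baseline rates from 0.26 to 0.95, every comparison of proportions tried that came close to 128 (126 to 131) needed a baseline of about 0.43 or more. That suggests a common outcome but is not proof. A two-group comparison of means with a standardised difference of 0.5 gives 2·(1.96 + 0.8416)²/0.5² ≈ 62.8, so 63 per group and 126 in total. That is equally close and uses no admission rate at all.

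**Odds ratio for a given risk ratio.** With reference risk p0 and p1 = RR·p0, OR = [p1/(1 − p1)] / [p0/(1 − p0)]. For a true RR of 1.5:

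| Assumed p0 | p1 | OR | OR/RR |
|---|---|---|---|
| 0.05 | 0.075 | 1.54 | 1.03 |
| 0.10 | 0.15 | 1.59 | 1.06 |
| 0.20 | 0.30 | 1.71 | 1.14 |
| 0.30 | 0.45 | 1.91 | 1.27 |
| 0.40 | 0.60 | 2.25 | 1.50 |
| 0.50 | 0.75 | 3.00 | 2.00 |

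At p0 = 0.50, for example, (0.75/0.25)/(0.50/0.50) = 3.00.

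The same happens below 1. A true RR of 0.75 is an OR of 0.73 at 10%, 0.68 at 30% and 0.60 at 50%.

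In the other direction, an OR of 2.0 at a reference risk of 50% means p1 = (2·0.5)/(0.5 + 2·0.5) = 0.667, a risk ratio of only 1.33.

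**With covariate adjustment.** One simulated dataset (200,000 records, a binary exposure, one continuous covariate, event rate above 50%) was analysed three ways. The adjusted logistic odds ratio was 1.97. Marginal standardisation of the same logistic fit gave a risk ratio of 1.29, and modified Poisson regression also gave 1.29. Both routes to a risk ratio agree, and both are far from the logistic coefficient.

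**The case against.** The strongest reply is that the two halves of the sentence can both be honoured. A logistic fit does yield adjusted risk ratios by marginal standardisation, and a condensed article may leave that step to a fuller document. It stands to this extent: the pairing is not impossible, and a reader who infers that odds ratios will certainly be published as risk ratios goes beyond the text. It does not remove the point. The article itself fixes both model and measure, sets them alongside linear regression and its native coefficient, and gives no sign that anything but the native output is meant.

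A second reply is that the main result is untouched. That is correct. Admission incidence would be reported as a frequency and percentage, and the issue reaches only the adjusted associations.

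A third is that the size rests on an assumed admission rate. That is also correct, and the range is shown for that reason.

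Two stronger readings are tempting. A reader might infer that mislabelled estimates could not be compared with the risk ratios cited in the Introduction. The documents do not support this as a harm. The cited risk ratios are contrasts of CGA in randomised trials, whereas this cohort follows only people who receive ED-CGA and no comparison group is described. Its adjusted estimates would not be comparable with those figures on any scale. A reader might also infer that associations with reattendance and readmission would be badly exaggerated. No rates are given for those outcomes, and at 10% to 20% the gap is modest.

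**Conclusion.** The point holds as a mismatch between the stated model and the stated effect measure. If odds ratios are reported under the RR label, adjusted associations will look further from 1 than the true risk ratios, by an amount that depends on how common the outcome is. For a true risk ratio of 1.5, the overstatement is about 6% at a reference risk of 10% and twofold at 50%. For admission the gap is likely to be large, on the assumption that admission is common in this at-risk older population; the sample size of 128 points that way without fixing a rate. For rare secondary outcomes it is small. The direction of associations, the crude admission incidence, the sample size and the data collection are not affected. This should be corrected in the analysis section, but it does not undermine the study's design.

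**What to change.** For binary outcomes, name one method that delivers the promised measure:

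- a modified Poisson model (log link, robust variance), or a log-binomial model, reporting adjusted risk ratios with 95% CIs; or
- the logistic model as planned, followed by marginal standardisation, with delta-method or bootstrap 95% CIs for the risk ratio.

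If neither is wanted, change 'adjusted RR' to 'adjusted OR' and describe the estimates as odds ratios throughout the report. The linear regression half of the sentence can stay.

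The cost is one sentence in the Statistical analyses section and, for the first two options, one changed or added model step. No new data are needed, and the change can be made before the analysis is run.
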